# Native opportunities to stop hypertension: study protocol for a randomized controlled trial among urban American Indian and Alaska Native adults with hypertension

**DOI:** 10.3389/fpubh.2023.1117824

**Published:** 2023-06-02

**Keywords:** American Indian/Alaska Native, dietary approach to stop hypertension, cardiovascular disease, blood pressure, health disparities, urban health, telenutrition, healthy diet

## Abstract

**Introduction:**

American Indian and Alaska Native (AI/AN) adults experience disproportionate cardiovascular disease (CVD) morbidity and mortality compared to other races, which may be partly attributable to higher burden of hypertension (HTN). Dietary Approaches to Stop Hypertension (DASH) is a high-impact therapeutic dietary intervention for primary and secondary prevention of CVD that can contribute to significant decreases in systolic blood pressure (BP). However, DASH-based interventions have not been tested with AI/AN adults, and unique social determinants of health warrant independent trials. This study will assess the effectiveness of a DASH-based intervention, called Native Opportunities to Stop Hypertension (NOSH), on systolic BP among AI/AN adults in three urban clinics.

**Methods:**

NOSH is a randomized controlled trial to test the effectiveness of an adapted DASH intervention compared to a control condition. Participants will be aged ≥18 years old, self-identify as AI/AN, have physician-diagnosed HTN, and have elevated systolic BP (≥ 130 mmHg). The intervention includes eight weekly, tailored telenutrition counseling sessions with a registered dietitian on DASH eating goals. Intervention participants will be provided $30 weekly and will be encouraged to purchase DASH-aligned foods. Participants in the control group will receive printed educational materials with general information about a low-sodium diet and eight weekly $30 grocery orders. All participants will complete assessments at baseline, after the 8-week intervention, and again 12 weeks post-baseline. A sub-sample of intervention participants will complete an extended support pilot study with assessments at 6- and 9-months post-baseline. The primary outcome is systolic BP. Secondary outcomes include modifiable CVD risk factors, heart disease and stroke risk scores, and dietary intake.

**Discussion:**

NOSH is among the first randomized controlled trials to test the impact of a diet-based intervention on HTN among urban AI/AN adults. If effective, NOSH has the potential to inform clinical strategies to reduce BP among AI/AN adults.

**Clinical trials registration:**

https://clinicaltrials.gov/ct2/show/NCT02796313, Identifier NCT02796313.

## Introduction

1.

American Indian and Alaska Native (AI/AN) people experience a disproportionate prevalence of cardiovascular disease (CVD) morbidity and mortality compared to other races (1, 2). CVD is the term for all types of diseases that affect the heart or blood vessels, including coronary heart disease (CHD), which can cause heart attack, stroke, heart failure, and peripheral artery disease (3). CHD prevalence rates among AI/AN people are greater than 12% (4) and may be underreported by 21% (5). The prevalence of CHD is particularly high among younger AI/AN people where more than one-third of deaths occur before the age of 65 years (6). Similarly, deaths due to stroke are the highest among younger AI/AN adults <45 years of age compared with other racial and ethnic groups in the United States (4).

Hypertension (HTN) is a major independent risk factor for the development of CHD and stroke (7, 8). A healthy diet can improve HTN management with or without medication (9–11) while also conferring other benefits, such as weight loss and healthier lipid profiles (12–15). Dietary Approaches to Stop Hypertension (DASH) is a high-impact therapeutic dietary intervention for primary and secondary prevention of CVD and is recognized as an effective dietary intervention to reduce blood pressure (BP) (16, 17). The DASH diet encourages low intakes of sodium and saturated fat paired with high intakes of fruits and vegetables. In a randomized trial, the DASH diet lowered systolic BP among participants with both borderline and clinical HTN (18). Despite a high prevalence of CVD-related morbidity and mortality and the effectiveness of the DASH diet to improve BP control across multiple studies, AI/AN people are noticeably absent in the research conducted to date.

AI/AN people interact with a unique healthcare system that may, in part, contribute to CVD inequities. The United States government provides healthcare to members of federally recognized Tribes through a treaty-based responsibility that has been filled by the Indian Health Service (IHS) since 1955. However, in reality, AI/AN people obtain healthcare through a fragmented process that includes IHS, Tribal, and urban Indian healthcare facilities, as well as public, private, and state-operated health initiatives. Notably, all IHS facilities are located on or near reservations, making many of them geographically inaccessible to most AI/AN people living in urban areas (19). Unsurprisingly, AI/AN adults often report more difficulties in healthcare access than White adults and have lower rates of healthcare utilization (20). Further, the IHS has been chronically underfunded, with $3,332 spent per patient per year in comparison to $9,207 per patient for federal health care nationwide (21). Despite the efforts of many Native nations to exert sovereignty and provide culturally-relevant care that incorporates both Western and traditional medicines, the complex configuration of healthcare systems, along with the policy and regulatory environments in which they operate, can adversely affect the ability of AI/AN people to obtain high-quality healthcare in Tribal and urban settings (22, 23).

Nationwide, AI/AN communities have lost access to traditional foods (24), which were historically nutrient dense and minimally processed. Furthermore, as AI/AN adults often have lower incomes than the general population, their ability to purchase healthy foods is limited (25, 26). AI/AN households are at greater risk of experiencing food insecurity, wherein a nutritionally-balanced diet is not geographically available or financially accessible, with prevalence rates ranging from 16 to 80% (27). Food insecurity is related to greater risk of HTN (27–30), and dependence on processed foods that increase sodium intake can further elevate risk (31–34). These barriers to access of healthful and affordable food options can, in part, be addressed through education and the increasingly common clinic-based food assistance programs that can involve medically-tailored groceries or food vouchers (35, 36).

Three key attributes are important for an intervention to successfully address HTN disparities experienced by AI/AN adults. First, an intervention must consider the needs of AI/AN adults in urban settings. Few studies have examined rates of HTN in urban AI/AN adults (37). Notably, most observational and intervention studies of CVD have focused on reservation-based AI/AN people, who receive care through the IHS and Tribally-run clinics, even though 71% of AI/AN adults live in urban areas (38). This urban population is an invisible minority (39), with high rates of disease and disability, low rates of healthcare usage (26, 40–42), and elevated risk of food insecurity (43–45). Second, CVD prevention through dietary practices should be a primary focus of a BP management intervention. Pharmacologic interventions can improve control of HTN and other CVD risk factors, but medications alone are sub-optimal and AI/AN adults with HTN are less likely than other racial groups to take anti-hypertensive medications (46). Further, medications do not address poor nutrition as a potential root cause of HTN. Benefits of the DASH diet have been demonstrated in primarily White and Black populations, but the DASH diet has never been tested with AI/AN participants. Given the unique historical and modern influences on the health of AI/AN communities, independent trials testing the effectiveness of interventions with AI/AN participants are warranted. Finally, an intervention needs to be relatively low cost to maximize accessibility and reach. One randomized trial of a clinic-based intervention in rural, AI/AN adults with diabetes showed that intensive BP management slowed or even reversed carotid intima-media thickening (47, 48). However, this approach is prohibitively expensive and logistically demanding for patients who lack adequate health insurance, reliable transportation, or ready access to care, all of which are common challenges for urban AI/AN adults.

The Native Opportunities to Stop Hypertension (NOSH) intervention is formulated after a recent DASH-based intervention, “Five Plus Nuts and Beans,” designed for urban Black adults, who experience many of the same barriers to healthy diet as urban AI/AN adults. In the Five Plus Nuts and Beans intervention, 120 participants were randomized to receive educational material on the DASH diet plus a weekly stipend for grocery delivery (control), or to receive DASH-oriented nutritional counseling and support from a registered dietitian (RD) plus a weekly stipend for heart-healthy grocery delivery (intervention). Participants in the intervention reported increased fruit and vegetable consumption and had improved urine potassium and sodium (49). Modeled after this intervention, the NOSH intervention includes a culturally-tailored DASH telenutrition curriculum that: emphasizes low sodium intake; emphasizes consumption of available traditional AI/AN foods; facilitates problem solving and provides strategies for maintaining healthy eating habits; and offers eight $30 weekly grocery orders. Traditional AI/AN foods, such as corn, salmon, trout, beans, and squash, are ubiquitous in contemporary grocery stores. However, recognition and acknowledgement that commonly stocked foods in grocery stores have their origins with Indigenous people is rare. By adapting various aspects of the Five Plus Nuts and Beans program and strong evidence-based dietary recommendations, the probability of effectiveness is increased.

Despite the growing number of urban AI/AN adults and longstanding disparities in CVD prevalence, no clinical trial has tested a therapeutic dietary intervention aimed to improve BP control among AI/AN with physician-diagnosed HTN. Thus, the NOSH study will evaluate an RD-delivered, adapted DASH intervention with urban AI/AN adults who receive care at one of three urban Indian clinics. In the NOSH intervention, weekly grocery orders will be complemented by nutrition counseling to promote locally-available food sources and motivate participants to adopt the DASH eating plan. This paper describes the NOSH randomized controlled trial to improve BP control among AI/AN adults. This study was approved by the Washington State University Institutional Review Board (#16118), the University of Oklahoma Institutional Review Board (#665427) and the Chickasaw Nation Institutional Review Board and has been registered with ClinicalTrials.gov (NCT02796313).

## Materials and methods

2.

### Study aims

2.1.

The NOSH study aims are to: (1) evaluate the effect of the NOSH intervention on BP and secondary outcomes in urban AI/AN adults with HTN; and (2) conduct a pilot study after the intervention concludes to evaluate extended support from an RD for an additional 6 weeks among a subset of participants. NOSH is a randomized, wait-list control trial (Figure 1). After completion of the two baseline visits, participants will be randomized into either the intervention or waitlist control group. Waitlist control condition participants will receive a brochure about the benefits of a low-sodium diet and complete weekly phone calls to collect BP readings and place grocery orders. After completion of data collection (12-months post-baseline), participants will be offered the intervention. The intervention group will receive the intervention and groceries (described in 2.6). At week 8, if participants are interested in participating in the pilot study, they will be randomized into either the pilot study control or extended support (intervention) groups. It is hypothesized that NOSH will result in improved BP management and secondary outcomes compared to the control condition. For the extended support pilot study, it is hypothesized that BP will attenuate toward baseline in both groups of the pilot study, but extended support will lead to more sustained improvement. The study design used to address these aims is shown in Figure 1.

**Figure 1 fig1:**
[figure not shown]
Native Opportunities to Stop Hypertension (NOSH) randomized controlled trial flow diagram and projected sample sizes.

### Setting

2.2.

The trial will be implemented in two urban clinics in Washington state and one urban clinic in Oklahoma. Urban AI/AN communities vary in food-related cultural norms and values, as well as in local resources for obtaining healthy food; therefore, the inclusion of three sites will support generalizability of results and feasibility of dissemination across multiple diverse sites. One Washington clinic recently recorded annual visits from 400 unique HTN patients, while the other Washington clinic recently recorded 704, and the Oklahoma site recorded 1,897 patients; all sites serve at least 100 new patients with HTN annually. The NOSH study uses a participatory research approach to ensure the intervention is feasible within clinics and relevant to participants and that research findings will benefit the study populations (50). Across all sites, this study leverages the expertise of community-based nutrition and dietetics practitioners who each have direct practice experience within these AI/AN communities.

### Participants

2.3.

#### Sample size

2.3.1.

Data from previous DASH interventions (51, 52) was used to estimate a sample size of 185 participants per group required to detect at least a 5.3 mmHg difference in mean systolic BP at 8 weeks, and a 5.7 mmHg difference in the 12-week analysis excluding the 25 extended support pilot study participants. Power of 80%, alpha error rate of 0.05, and a standard deviation of 18 mmHg based on previous 8- or 9-week trials were assumed.

#### Recruitment

2.3.2.

A total of 370 participants will be recruited (approximately 120 from each site) with equal representation of men and women. At each clinic, separate lists of men and women in the target age range with physician-diagnosed HTN and at least two systolic readings ≥130 mmHg will be created. Each list will be randomly sequenced by the study biostatistician. Starting at the top of the lists, the research team will work with clinic staff to review medical charts for additional eligibility criteria. For patients who meet eligibility criteria, study staff will contact the primary care provider to secure approval for participation. Patients will be contacted by telephone and/or in-person at their next clinic visit to ascertain interest about the study and confirm eligibility. Eligible individuals will be scheduled for an initial baseline visit, ideally within 2 weeks of the in-person contact. Final determination of eligibility will occur at the second baseline visit based on an additional BP measure and compliance with study protocols (described below).

#### Eligibility criteria

2.3.3.

Participants must: (1) be at least 18 years old; (2) have had a clinical diagnosis of HTN for at least 1 year; (3) be on a stable regimen of antihypertensive medications for a minimum of 2 months OR not currently medicated, without anticipated changes for the duration of the study; (4) have average systolic BP ≥ 130 mmHg at the past two clinic visits and at the in-person screening visit; (5) have regular medical care and permission from their primary care provider to participate; (6) be physically and cognitively able to use the home BP monitoring device; and (7) be willing and able to follow all other study procedures. People will be ineligible if they: (1) experienced incident CVD or stroke within the previous 6 months; (2) have average diastolic BP ≥ 100 mmHg during the run-in period; (3) have a known diagnosis of secondary HTN (e.g., renal artery stenosis); (4) have diagnosed Stage 4 or 5 kidney disease; (5) have a recent history or high blood potassium due to taking certain medications that can raise potassium levels; (6) are participating in another health research study; (7) are currently or planning to become pregnant during the course of the study; or (8) are receiving treatment for cancer or another serious or terminal medical condition.

#### Consent

2.3.4.

The in-person screening will take place at the first baseline visit, which will occur within 2 weeks of initial screening for eligibility and interest. A research assistant will describe the study and risks of participation. The site study coordinator will also review the study and measure BP. For people whose average BP is within eligibility limits, the site study coordinator will administer the full informed consent protocol, explaining study goals, procedures, and potential risks, in addition to requesting Health Insurance Portability and Accountability Act (HIPAA) authorization to allow ongoing access to their medical records (HIPAA is meant to protect a patient from having their information disclosed without the individual’s consent or knowledge). Clinic staff will enter information pertinent to the patient’s care in the medical record notes as it is deemed appropriate and will document provider approval to participate in the study. These notes will be left to the discretion of clinic staff and will not be shared with the study team. Participants will provide written informed consent and HIPAA authorization.

For the extended support pilot study, at the 8-week appointment, while intervention group participants are completing their follow up data collection, the research assistant will access the next assignment on a randomized list created by the study biostatistician. If intervention group participants are interested in participating in the pilot study, they will undergo an additional informed consent process and be further randomized to one of the following two groups: (1) pilot study control, or (2) extended support (pilot study intervention). Potential participants will be clearly informed that their choice whether to participate in the pilot study will not affect their participation in the 12-week follow-up for the main trial.

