### Assessment procedures

2.4.

Participants will complete four clinic visits (screening/baseline 1 visit, baseline 2 visit, week 8, and week 12) for the study. Two baseline visits are conducted to: (1) minimize the length of clinic visits by collecting surveys and clinical data on two separate dates, and (2) as a way of assessing compliance with study protocols. Participants are provided 24-h urine collection materials and the home BP monitor at the end of the first baseline visit. If they have completed the at-home urine and BP data collection when they return for the second baseline visit, they are considered compliant with study protocols. Compensation will be in the form of gift cards to local gas stations or grocery stores in the following amounts: second baseline visit ($50), 8- and 12-week visits ($50 each).

For the extended support pilot study, telephone interviews will be conducted to collect home BP data using the same study-provided devices at six and 9 months post-baseline. About 5 months post-baseline, pilot study participants will be contacted to schedule the 6-month data collection interview and provide re-training in use of the home BP cuff, if necessary. The 6- and 9-month interviews will be conducted by telephone by research staff who are masked to treatment group assignment. Staff will talk each participant through the process of accessing BP values stored in the cuff’s memory. Participants will read off values, and staff will enter them into a study database. Phone conversations will be recorded as electronic data files and erased after quality control checks have been completed.

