### Randomization

2.5.

Treatment conditions will be randomly assigned after the participant completes the clinical data collection at the second baseline visit. The study staff will generate treatment assignments using the randomization function in the study’s REDCap database.

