### Intervention

2.6.

The DASH diet is low in saturated fat, cholesterol, and total fat, focuses on fruits, vegetables, and fat-free or low-fat dairy products, and is rich in whole grains, fish, poultry, beans, seeds, and nuts. It minimizes intake of ultra-processed foods, including sweets, added sugars, and sugary beverages, as well as red meats compared to the typical American diet. Its unique composition of prescribed food groups results in a nutrition profile that is lower in sodium and rich in potassium, magnesium, and calcium. The intervention group will receive one in-person, tailored nutrition counseling visit at baseline and weekly 15-min telenutrition sessions in weeks 2–8 to provide additional DASH diet education and behavior change support.

After the final DASH session is complete, a questionnaire will be mailed to the participant in order to evaluate their satisfaction with the program. The 14-item anonymous questionnaire asks participants to rate their degree of agreement with statements such as, “The information about the DASH diet was easy to understand,” “It is difficult for me to do exactly what the nutrition staff recommended,” and “I will be able to follow the DASH diet and nutrition staff’s advice after the program.” Additional questions ask what participants liked about the program, what could have been improved or changed, what activities or information was most useful, and what diet and lifestyle changes were the most difficult to change.

During the extended support pilot study, the 25 intervention participants receiving extended support will continue to receive weekly 15-min phone consultations with the RD for an additional 6 weeks (weeks 9–14) after the end of the original 8-week study period. Consultations will provide support for continuing the DASH diet and will focus on overcoming barriers to obtaining and preparing healthy foods within the context of each person’s regular food budget and resources.

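### The extended-support pilot opens the next assignment before interest and consent, so the Aim 2 comparison is exposed to selection bias; the 8-week primary outcome is not

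*Protocol article*

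**What the plan says.** The Consent section (2.3.4) describes pilot entry at the 8-week appointment. The first step given is that, "while intervention group participants are completing their follow up data collection, the research assistant will access the next assignment on a randomized list"; the list comes from the study biostatistician. The next sentence reads: "If intervention group participants are interested in participating in the pilot study, they will undergo an additional informed consent process and be further randomized". Joining is optional, since participants are told that "their choice whether to participate in the pilot study will not affect their participation in the 12-week follow-up for the main trial".

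Study aims (2.1) gives a shorter account: "At week 8, if participants are interested in participating in the pilot study, they will be randomized into either the pilot study control" or the extended-support group.

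For the main trial, Randomization (2.5) says: "Treatment conditions will be randomly assigned after the participant completes the clinical data collection at the second baseline visit". It adds: "The study staff will generate treatment assignments using the randomization function" in the study's REDCap database.

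The only masking stated for the pilot is in Assessment procedures (2.4): "The 6- and 9-month interviews will be conducted by telephone by research staff who are masked to treatment group assignment". The Intervention section (2.6) puts the size of one pilot arm at "the 25 intervention participants receiving extended support".

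**The concern.** Concealment means that nobody who can influence enrolment knows the next assignment until the participant is irrevocably in. The order written in 2.3.4 does not secure this. The assignment is accessed first, and interest and consent follow. Someone at the visit may know whether the next entrant would get six more weeks of dietitian calls or none, and that knowledge can colour how warmly the pilot is presented and to whom.

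If willingness to join then depends on prognosis differently for the two assignments, the pilot arms differ at entry for reasons other than chance. Part of the difference may show in 8-week systolic BP, which is measured and can be adjusted for. The rest, such as motivation or expected adherence, does not show there and cannot be recovered in analysis. At stake is the second of the two study aims, which carries its own directional hypothesis. Masked telephone interviewers at 6 and 9 months protect how the outcome is assessed, not who enters each arm.

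**Working it through.** The plan gives no figure on this point, so the main check is the order of steps.

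| Step | Pilot (2.3.4) | Main trial (2.5) |
|---|---|---|
| Assignment accessed or generated | While 8-week data collection is under way | After clinical data collection at the second baseline visit |
| Source | List prepared by the biostatistician, accessed by the research assistant | REDCap randomization function |
| Interest and consent | Mentioned after access to the list | Consent is administered at the first baseline visit, before assignment |
| Concealment described | None | Assignment does not exist until generated |

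Study aims (2.1) makes randomization conditional on interest but is silent on whether the list stays unread until then. The phrase in 2.3.4 about being further randomized after consent is silent on it too. Neither reverses the stated early access.

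**Which outcomes can be reached.** Primary outcome (2.8) defines the endpoint as home systolic BP, taken by the participant over the 7 days before each visit. The 8-week readings therefore precede the appointment at which the list is accessed. Measures made at that appointment, such as auscultated clinic BP (2.9.1) or the assisted dietary recall (2.9.4), could in principle be taken with the pilot assignment known.

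**Illustration of size.** These inputs are assumptions except the standard deviation, which Sample size (2.3.1) gives as 18 mmHg for the main trial and which is borrowed here for prognosis.

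- Standardized prognosis Z is normal with mean 0 and variance 1.
- The two assignments are equally likely.
- When pilot control is next, consent is 50% whatever Z is.
- When extended support is known to be next, the consent probability is p(Z) = 1/(1 + exp(−tZ)), where t is the log-odds slope per standard deviation. The average is still 50%.

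Mean prognosis among consenters is 0 for pilot control. For extended support it is E[Z·p(Z)] / E[p(Z)] = 2·E[Z·p(Z)] = 2·t·E[p(1 − p)]. The spurious difference is 18 times that.

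| Slope t | E[p(1 − p)] | Shift in SD | Difference, mmHg |
|---|---|---|---|
| 0 | 0.250 | 0 | 0 |
| 0.25 | 0.246 | 2 × 0.25 × 0.246 = 0.123 | 2.2 |
| 0.5 | 0.236 | 2 × 0.5 × 0.236 = 0.236 | 4.2 |
| 1.0 | 0.207 | 2 × 1.0 × 0.207 = 0.413 | 7.4 |

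A simulation with 2,000,000 draws agrees to within 0.1 mmHg. If the assignment is unknown until consent, the same slope acts on both arms alike and the expected difference is 0 at every t.

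The table gives differences before any adjustment. It shows the mechanism and a plausible range; it does not estimate what will happen in this trial.

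**The case against.** The strongest reply is that the text can be read more kindly. Accessing an assignment might mean having it ready, not reading it, with formal allocation after consent, as 2.1 and the later words of 2.3.4 suggest. The document does not say that the assistant who accesses the list also seeks pilot consent; in the main trial the assistant describes the study and the site study coordinator administers consent. The article is condensed, and a release mechanism may be set out in a fuller protocol. This stands to the extent that a breach of concealment is permitted by the text, not proven. It does not remove the point, because the order of steps is stated rather than left out, and it places access first.

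Three stronger readings are tempting and are not supported:

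- A reader might infer that the main trial's 8-week primary outcome is compromised. It is not: those home readings are taken before the list is accessed.
- A reader might infer that an opened assignment is discarded, or passed on as a known allocation, when someone declines. The document does not say what happens then.
- A reader might infer that the pilot comparison is beyond repair in analysis. Imbalance in measured 8-week systolic BP can be adjusted for; only the unmeasured part cannot.

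A reader might also look to the 12-week main analysis, since Data analysis (2.12) drops the 25 extended-support participants. That exclusion removes volunteers even under perfect concealment, so it is a separate matter. Its scale is modest: if the 25 differ by an assumed 2 mmHg from the other 160 (185 − 25), dropping them moves the arm mean by 25 × 2 / 185 ≈ 0.3 mmHg, against the stated detectable difference of 5.7 mmHg.

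**Conclusion.** The point holds for the pilot. The protocol states an order in which the next pilot assignment is accessed before interest and consent, describes no concealment, and departs from the sequence used in its own main trial. The Aim 2 comparison is therefore open to selection bias, only partly removable by adjusting for 8-week systolic BP.

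The size cannot be derived from the documents. The range of about 2.2 to 7.4 mmHg rests on assumed consent slopes, an assumed 50% consent rate and a borrowed standard deviation of 18 mmHg. The conclusion needs only that accessing the list lets someone at the visit learn the assignment and affect who joins, which the text neither states outright nor prevents.

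Severity is moderate. The 8-week primary comparison stands; among the 8-week data, only measures taken in clinic at that visit could be touched.

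**What to change.** Rewrite the pilot-entry sentence in 2.3.4 so that the order is explicit:

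1. All 8-week measurements are completed.
2. Interest and written pilot consent are recorded.
3. Only then is the assignment released, through a mechanism that staff at the visit cannot read in advance. The REDCap randomization function already used in the main trial would serve.

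Bring 2.1 into line by saying that randomization follows consent. If a fuller protocol already works this way, correcting the sentence is enough.

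The cost is one procedural sentence and one REDCap randomization form, with no added visits or staff. It should be in place before pilot enrolment, because unmeasured selection cannot be undone afterwards. If pilot enrolment has already begun, report the sequence actually followed, together with refusals by assignment where these were recorded.
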